#### Moderators

To examine the characteristics of participants for whom the intervention is most efficacious, we will include measures at baseline of perceived barriers to treatment, PTSD symptoms, depression symptoms, and AUD severity. Perceived barriers are assessed with the 15-item RAND Barriers to Mental Health Care item bank [70]. Items are rated on a scale from 1 (not at all) to 5 (very much) and reflect barriers of perceived stigma (eg, seeking care would be viewed as a sign of personal failure, others would lose respect for the person, and other veterans would see them as weak), fears about confidentiality (eg, people might find out about it), beliefs that treatment does not work, and difficulties finding time for treatment due to other responsibilities (eg, because of work or family). These items can be summed to receive a baseline severity of barriers score. PTSD symptoms will be assessed with the 20-item PTSD Checklist (PCL-5), a widely used measure for military and veteran populations with adequate reliability and validity for young adult military samples [71]. Depression symptoms will be assessed with the Patient Health Questionnaire 8-item (PHQ-8), a reliable and valid measure of depression used in research and practice for military and veterans [72-74]. The severity of AUD will be assessed with the AUDIT [54], a 10-item alcohol screen that identifies individuals who had probable AUD in the past year. The PCL-5, PHQ-8, and AUDIT can each be summed to create baseline symptom severity scores for each.

### Analytic Plan

#### Overview

Prior to the main aims analyses, we will assess for multivariate normality. The maximum likelihood estimator will be used if data are approximately normal and robust maximum likelihood will be used if the data are not multivariate normal. Missing data will be assumed to be missing at random and handled using direct maximum likelihood techniques. We will assess for differences in baseline demographics and military characteristics between the intervention (BRAVE) and control conditions. Any characteristic significantly different between groups will be controlled for in analyses.

To assess the effects of the intervention on continuous primary outcomes (drinking days, average drinks per occasion, binge drinking days, negative alcohol-related consequences, and treatment initiation) and secondary outcomes (preparatory behaviors, readiness to seek care ruler for alcohol, readiness to seek care ruler for mental health), a taxonomy of latent growth models will be estimated [75]. The primary outcome time point for this trial will be the baseline to first follow-up (ie, 3 months post baseline); however, we are interested in the past 30-day changes from baseline to each of the 3 additional follow-up timepoints (ie, baseline to 6, 9, and 12 months post baseline). To assess between-group differences in the intercept and growth factors, we will regress each on a dummy variable representing the intervention (BRAVE=1) and control (control=0) groups. For any count variables, negative binomial or Poisson distributions will be explored for better model fit. To understand the change in treatment initiation (binary outcome), we will use latent growth models with categorical outcomes, as well as estimate simple logistic regression at each time point. To understand the practical significance, we will calculate standardized mean differences (Cohen *d*) at all 4 follow-up time points for both between group and within group.

We will test for significant effect moderation by the following variables: barriers to care, PTSD, depression, and severity of AUD symptoms. To explore moderation, we will use simple linear regression models for primary outcomes at each time point. We will include an interaction term between each potential moderator and the intervention indicator (BRAVE vs control). Significant interactions between the intervention group and these moderators will be plotted with appropriate values and interpreted. Simple slopes will be calculated for all significant interactions. Given our prior work and the large sample size, we expect to have adequate numbers of participants in each cell for moderation analyses and will use established cutoff scores on the PCL-5 (score 33 or higher vs under 33), PHQ-8 (scores 10 or higher vs under 10), and the AUDIT (scores 8 or higher vs under 8). We hypothesize that those with greater barriers, PTSD, depression, and severity of AUD symptoms will benefit most from the intervention. Sex (male or female) will be included as an exploratory moderator.

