**Methods:**

We will conduct an RCT with 800 post-9/11 young adult veterans (aged 18 to 40 years) with potentially hazardous drinking and who have not recently received treatment for any behavioral health problems. Participants will be randomly assigned to the personalized intervention or a control condition with resources for seeking care. The personalized normative feedback module in the intervention focuses on the correction of misperceived norms of peer alcohol use and uses empirically informed approaches to increase motivation to address alcohol use and co-occurring behavioral health problems. Past 30-day drinking, alcohol-related consequences, and treatment-seeking behaviors will be assessed at baseline and 3, 6, 9, and 12 months post intervention. Sex, barriers to care, posttraumatic stress disorder, depression, and severity of alcohol use disorder symptoms will be explored as potential moderators of outcomes.

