#### Demographics and Background

Participants will fill out several demographic items that will be used to describe the sample. These include age, sex at birth, gender, race, ethnicity, income level, military branch, military rank and pay grade at discharge, number and location of deployments, education level, marital status, and number of children. Participants will also complete a measure of combat exposure to assess for presence and severity of combat experiences while in the military [27].

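### Covariates are chosen by significance tests of chance baseline differences instead of being named in advance; the precision lost falls mainly on the single-wave regressions.

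*Protocol article*

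**What the plan says.** The Overview of the Analytic Plan sets the rule in two sentences. The first defines what is tested: "We will assess for differences in baseline demographics and military characteristics between the intervention (BRAVE) and control conditions". The second says what follows: "Any characteristic significantly different between groups will be controlled for in analyses". No covariate is named in advance for any main model.

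The candidates are listed under Demographics and Background, which opens: "Participants will fill out several demographic items that will be used to describe the sample". The list begins "These include age, sex at birth, gender, race, ethnicity, income level, military branch, military rank and pay grade at discharge" and continues with deployments, education, marital status and number of children; a combat exposure measure is added.

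The models to which the rule applies are:

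- **Drinking, consequences and secondary outcomes:** "a taxonomy of latent growth models will be estimated", with arm entering as follows: "To assess between-group differences in the intercept and growth factors, we will regress each on a dummy variable". The contrast of interest is change from baseline: "The primary outcome time point for this trial will be the baseline to first follow-up (ie, 3 months post baseline".
- **Treatment initiation (binary, primary):** a categorical growth model, plus a simple logistic regression at each time point.
- **Moderation (second aim):** simple linear regressions of the primary outcomes at each time point, with a moderator-by-arm interaction.

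The outcomes are measured at every wave: "Past 30-day drinking, alcohol-related consequences, and treatment-seeking behaviors will be assessed at baseline and 3, 6, 9, and 12 months". AUDIT, PCL-5, PHQ-8 and barriers are also measured at baseline, but the plan gives them a role only as moderators (AUDIT also sets eligibility).

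**The concern.** Randomisation makes any baseline difference between arms a chance event. A significance test of that difference says nothing about whether the variable predicts outcome, which is what decides whether adjustment helps. Three things follow.

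1. The covariate set depends on the data. Whether a model is adjusted, and for what, becomes known only once the arms have been compared.
2. The screen covers the wrong variables. It is confined to demographic and military items, so AUDIT, PHQ-8, PCL-5 and readiness cannot enter the main models through it, however prognostic or imbalanced they are.
3. Precision is lost where the model has no other use of baseline information, namely the regressions fitted to one wave at a time.

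Precision matters here. The Power Analysis gives a detectable effect of d=0.22 at 3 months and cites pilot effects of 0.17 to 0.19 for reference, although it expects somewhat larger effects in this sample.

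**Working it through.** **Inputs from the article.** 400 randomised per arm; two-sided 0.05; 80% power; detectable d=0.22 (3 and 6 months) and 0.23 (9 and 12 months). Candidate characteristics: 13 if rank/pay grade and number/location of deployments each count once and combat exposure is included; up to 16 if those items are split and presence and severity of combat exposure count separately.

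**Assumed, because the article does not give them.** Number analysed per arm, and the correlation ρ between baseline and follow-up outcome.

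**1. The plan's own figure.** For two means with SD 1, n per arm = 2(1.960+0.842)²/d².

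- d=0.22: 15.70/0.0484 gives 325 per arm, or 325/400 = 81% retained.
- d=0.23: 15.70/0.0529 gives 297 per arm, or 74% retained.
- With all 400 per arm, the detectable effect is 0.198 and power at d=0.22 is 87.5%.

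The stated effects therefore fit an unadjusted comparison with roughly 80% and 75% retention. No retention rate is stated, so 325 per arm is an inference.

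**2. Chance that the screen selects something.** For k independent tests this is 1 − 0.95^k.

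- k=13: 48.7%, with 13 × 0.05 = 0.65 selected on average.
- k=16: 56.0%, with 0.80 selected on average.

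Sex and gender, or rank and pay grade, are clearly related, so the true figure is somewhat lower.

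**3. Error rate and precision of an adjust-if-significant rule.** Simulation: 20,000 trials, 325 per arm, one covariate with correlation r to the outcome, adjusted for only if its baseline test gives |t|>1.96.

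| r | Type I error: never / rule / always | SE: never / rule / always |
|---|---|---|
| 0.3 | 0.049 / 0.047 / 0.051 | 0.078 / 0.077 / 0.075 |
| 0.5 | 0.048 / 0.041 / 0.048 | 0.078 / 0.075 / 0.068 |
| 0.6 | 0.048 / 0.039 / 0.049 | 0.078 / 0.074 / 0.063 |

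The rule is mildly conservative. At r=0.5 it recovers about a quarter of the available gain: (0.0778−0.0751)/(0.0778−0.0675) = 0.26. This shows how such a rule behaves. It is not an estimate for this trial, since a demographic item is unlikely to correlate that strongly with drinking.

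**4. Single-wave continuous comparison, 325 per arm, d=0.22.** Variance factor 1 without adjustment; 1−ρ² with the baseline outcome as covariate.

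| ρ | Factor | Power adjusted | Power unadjusted |
|---|---|---|---|
| 0.4 | 0.84 | 86% | 80% |
| 0.5 | 0.75 | 90% | 80% |
| 0.6 | 0.64 | 94% | 80% |

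This applies to a linear model for a continuous outcome. It is not a figure for the logistic regressions.

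**5. What the growth models already capture.** For a five-wave linear growth model under compound symmetry, the variance factor for the 12-month change is 0.96, 0.80 and 0.64 at ρ=0.4, 0.5 and 0.6, against 0.84, 0.75 and 0.64 for baseline-as-covariate. Most of the baseline information is therefore in use at 12 months. For a bare two-wave change the factor is 2(1−ρ) = 1.2, 1.0 and 0.8, so the remaining gap depends on the form of growth model chosen. Adding AUDIT after baseline drinking would remove a further 1%, 4% or 9% of residual variance for an assumed partial correlation of 0.1, 0.2 or 0.3.

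**The case against.** The strongest reply is that the main analysis of drinking and consequences already uses baseline. A reader might infer from the covariate rule that baseline drinking is thrown away. The Analytic Plan does not support that: the growth models describe change from baseline, and the baseline survey is their first wave. This part of the reply stands.

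A reader might also expect data-driven adjustment to inflate false positives. The simulation shows the opposite, about 4% against a nominal 5%.

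Nor can the 86–94% in step 4 be read as the power the quoted sentence costs. The rule never screens the baseline outcome. For the demographic items it does screen, always adjusting helps little: with correlations of 0.1, 0.2 and 0.3 (variance factors 0.99, 0.96, 0.91), power at d=0.22 is about 80%, 82% and 84%, against 80% unadjusted.

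Two further points are fair. The moderation regressions are not empty of prognostic information, since AUDIT, PCL-5 and PHQ-8 each enter their own model as a moderator. And the logistic regressions accompany a categorical growth model.

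What the reply does not remove is the rule itself. It is stated text, so a fuller analysis plan would have to contradict it to repair it. For treatment initiation, the first wave helps little: eligibility excludes behavioral health appointments in the previous six months, so baseline values will vary little. They need not all be zero, because the outcome item also counts general medical providers, support groups and medications.

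**Conclusion.** The point holds as one about prespecification and precision, and is worth correcting before analysis. The covariate set is decided by chance imbalance, with a 49–56% probability of at least one selection under independence, and the screen leaves out the clinical measures collected at baseline. The cost falls mainly on the simple logistic regressions for treatment initiation and the linear moderation regressions, neither of which names a baseline outcome or any other prognostic covariate beyond the moderator under test. The growth models stand to gain less, chiefly from AUDIT.

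The size of the loss rests on an assumed 325 analysed per arm and assumed correlations of 0.4 to 0.6, and the power illustration covers continuous single-wave outcomes only. A reader might conclude that the stated power is wrong; it is not affected, since it does not appear to rely on covariate adjustment.

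**What to change.** Delete the sentence that makes adjustment depend on a significant baseline difference, drop the baseline tests, and report the baseline table descriptively. In its place, prespecify covariates that enter whatever imbalance is observed:

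- AUDIT and sex in the main models;
- the baseline value of the outcome in the single-wave linear regressions;
- a short named set of baseline prognostic measures, for example AUDIT, PHQ-8 and PCL-5, in the logistic regressions for treatment initiation.

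The exact list is a matter of judgement; what matters is that it is fixed before the arms are compared. The cost is a sentence or two in the analysis plan, and the data are already being collected. One small downside is that adjustment makes the logistic odds ratio conditional on the covariates, so the plan should say so or also report a marginal (standardised) risk difference.

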#### Primary Outcomes

Primary outcomes are drinking behavior (past 30-day frequency, quantity, and number of binge-drinking days), negative alcohol-related consequences, and treatment initiation. Three past 30-day drinking outcomes will be assessed through single-item self-reports: drinking days, average drinks per occasion, and binge drinking days. Alcohol-related consequences in the past 30 days will be assessed with the Short Inventory of Problems [68], which is modified from the Drinker Inventory of Consequences [69]. The treatment outcome will be measured as treatment initiation in the time period after the intervention (ie, post baseline). Treatment initiation is assessed with an item asking participants to indicate if they have seen a provider at a VA or non-VA care setting for therapy, counseling, support groups, hospitalization, or medications for any concerns related to alcohol or substance use (eg, if they sought help to drink less, or attended groups to stay abstinent from cannabis or other drugs) or mental health concerns (eg, to help with stress, anxiety, depression, nightmares) in the past 6 months (at baseline) and past 3 months (follow-ups). Providers are defined for participants as a mental health or behavioral health provider (eg, psychiatrist, psychologist, social worker, mental or behavioral health nurse, or other providers), a general medical provider (eg, primary care doctor, physician assistant, and nurse practitioner), or an addiction specialist (eg, addiction counselor). Care is specified as either in-person or via telehealth.

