#### Secondary Outcomes

The decision to seek care and then actual receipt of care can be a lengthy process. Given that participants may not receive any care during the 12 months of follow-up, we will also assess their readiness to receive care in the future and if they made preparations to receive that care. Preparatory behaviors will be specified as 6 behaviors participants would definitely do, probably do, probably not do, or definitely not do in the next 30 days to prepare for treatment (ie, looking at options on the internet; discussing with a partner, family member, or friend the options available; talking with a partner, family member, or friend about their experiences with treatment; contacting a provider to learn more about the options; contacting the insurance provider to see what options are available; and contacting a provider to make an appointment). Two readiness rulers will also assess participants’ readiness to seek care in the next 30 days in order to reduce their drinking and to address any mental health concerns they have from 0 (not ready at all) to 10 (absolutely ready).

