#### Power Analysis

Given this study design (and standard *P*<.05; 2-tailed testing), we will have 80% power to detect small treatment effects between the groups; specifically, effects of d=0.22 at 3- and 6-month follow-ups and d=0.23 at 9- and 12-month follow-ups. For reference, our observed intervention effect sizes at 1 month post intervention in the pilot study were *d*=0.17 for average drinks, *d*=0.18 for binge days per month, and *d*=0.19 for consequences [49]. We have similarly found small effect sizes over 2 years of follow-up in other large-scale PNF studies [76-78]. We expect effect sizes to be small, though slightly larger than those in our prior work given we include a sample screening positive for hazardous alcohol use that could benefit from treatment, whereas prior work targeted general college students and young veterans drinking at less severe levels. As noted, given that this intervention targets those who may never have received care otherwise, small effects seen in brief interventions, such as this, are potentially clinically significant.

Our prior work evaluating treatment-seeking behaviors has found rates of preparatory and actual treatment-seeking by service members to increase by double following brief phone-based feedback [79]. Other work has similarly found rates of substance use treatment initiation to increase to upwards of 50% following in-person feedback–based approaches [80]; thus, we hypothesize that upwards of 50% of participants who receive the enhanced PNF will report actual treatment initiation at some point during the 12-month follow-up period. We will examine preparatory behaviors (ie, steps along the way to actual initiation) and motivation to seek care.

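### From 6 months on, the past-3-month care item measures care use in that window, and no stated analysis addresses the 12-month treatment-initiation hypothesis

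*Protocol article*

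**What the plan says.** The protocol article's Primary Outcomes section lists drinking behaviour, "negative alcohol-related consequences, and treatment initiation". It defines the treatment outcome in general terms: "The treatment outcome will be measured as treatment initiation in the time period after the intervention (ie, post baseline". The item itself asks whether the participant has seen a provider "in the past 6 months (at baseline) and past 3 months (follow-ups".

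The Analytic Plan (Overview) fixes the time point without an exception for initiation: "The primary outcome time point for this trial will be the baseline to first follow-up (ie, 3 months post baseline". For initiation, "we will use latent growth models with categorical outcomes, as well as estimate simple logistic regression at each time point". No cumulative or time-to-first-care analysis is named.

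Three other sections bear on timing:
- Secondary Outcomes: "The decision to seek care and then actual receipt of care can be a lengthy process". It adds that some participants may receive no care within 12 months.
- Power Analysis: upwards of 50% of intervention participants "will report actual treatment initiation at some point during the 12-month follow-up period".
- Specific Aims and Hypotheses: more initiation than control at each of the four follow-up visits.

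**The concern.** Initiation is a first event: a person who was not in care starts care. Eligibility excludes anyone with behavioural health appointments in the previous six months or upcoming ones, so a yes at 3 months is a first start since baseline. After that the item and the concept part. A yes at month 6, 9 or 12 mixes new starters with people continuing care. A no mixes people who never started with people who started and finished before the window opened. The categorical growth model uses every visit, but it describes the trajectory of this same item.

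If results at later visits are reported as initiation, early success followed by completed care will look like decline. The only quantified initiation hypothesis, a 12-month cumulative one, would have no analysis of its own.

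**Working it through.** **The plan's own figures.** The Power Analysis gives d = 0.22 (3 and 6 months) and d = 0.23 (9 and 12 months) at 80% power, two-sided 5%. From n per arm = 2(1.96 + 0.8416)²/d²:
- d = 0.22 gives 324.3, so 325 per arm (325/400 = 81%).
- d = 0.23 gives 296.7, so 297 per arm (297/400 = 74%).

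Retention is not stated. All 400 per arm would give d = 0.198. The figures fit plausible attrition but cannot be confirmed, and they do not cover a binary outcome. I use 325 and 297 below as assumed analysed numbers.

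**Power, 3-month window against 12-month cumulative.** The 50% for the intervention arm is from the Power Analysis; control rates are my assumptions, since none is given. Under a constant hazard, initiation by 3 months = 1 − (1 − p₁₂)^(1/4). Power = Φ{[|p₁ − p₂| − 1.96√(2p̄(1 − p̄)/n)] / √([p₁(1 − p₁) + p₂(1 − p₂)]/n)}.

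For 50% against 40%:
- 3 months: 15.9% against 12.0%, (0.0392 − 0.0533)/0.0271 = −0.52, power 30%.
- 12 months cumulative: (0.100 − 0.0800)/0.0406 = 0.49, power 69%.

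| Assumed control 12-month rate | 3-month power | 12-month cumulative power |
|---|---|---|
| 40% | 30% | 69% |
| 38% | 41% | 84% |
| 35% | 58% | 96% |
| 30% | 82% | >99% |
| 25% | 95% | >99% |

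**Slower uptake.** Take 50% against 25%, with a share s of each arm's 12-month initiations falling in the first 3 months. For s = 5%, 10%, 15% and 25%, 3-month power is 22%, 39%, 55% and 78%. Cumulative power stays above 99%.

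**Early uptake.** Assume 20% against 10% initiate in quarter 1, then 10% of those remaining per quarter in both arms. New initiators are:
- Intervention: 20.0 + 8.0 + 7.2 + 6.5 = 41.7%
- Control: 10.0 + 9.0 + 8.1 + 7.3 = 34.4%

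Power is about 95% at 3 months (20% against 10%, n = 325) and about 45% for the cumulative comparison (n = 297).

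**What the month-12 item would show in that example.** Let r be the share of those in care in one window who are still in care in the next. Then window proportion = new initiators + r × previous window.

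| r | Intervention | Control |
|---|---|---|
| 0 | 6.5% | 7.3% |
| 0.5 | 14.6% | 14.8% |
| 0.75 | 24.8% | 22.6% |

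The cumulative lead of 7.3 points disappears or turns slightly negative unless most people stay in care. At r = 0 the power to detect the month-12 difference is only about 6%.

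A steeper assumed pattern has new initiators of 30, 10, 6 and 4% against 10% each quarter (cumulative 50% against 40%). It gives 4% against 10% at r = 0, 13.3% against 18.8% at r = 0.5, and 26.8% against 27.3% at r = 0.75.

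**The case against.** The case for the plan as written has real force.

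- **The visit-by-visit tests have a stated basis.** Specific Aims hypothesises differences at each visit. A reader might infer that the trial cannot test the initiation hypothesis it states. The documents do not support that: the planned tests address the aim's hypothesis, and the 3-month test addresses initiation itself. What stays without an analysis is the 12-month statement. That statement is worded as a one-arm expectation, but it is the only figure given for initiation.
- **Three months is not necessarily the wrong time point.** The Power Analysis cites a doubling in prior work. At 50% against 25% with a constant hazard, 3-month power is 95%. The Introduction describes normative-feedback effects as often short-lived. In the early-uptake example the 3-month test clearly beats the cumulative one.
- **The harms need opposite conditions.** Low 3-month power needs slow or evenly spread uptake. A late reversal needs early uptake and short care, and the qualifying care includes medications and support groups, which can continue. A reader might infer that the primary result will be missed or will look reversed; neither follows from the text.
- **Coding could be left to the full analysis plan.** The general post-baseline definition is compatible with cumulative coding. But the article does fix the recall window, the time point and the analyses, and together these do not yield cumulative initiation.
- **The remark on lengthy care-seeking is partly answered.** It is the stated reason for the readiness and preparatory outcomes. That does not change what the care item measures.

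**Conclusion.** The concern holds as a mismatch between outcome and analysis. At 6, 9 and 12 months the plan would analyse current care use under the name of initiation, and the 12-month hypothesis has no stated analysis. This rests on the text alone.

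The size rests on assumptions about control rates, uptake timing, care duration and analysed numbers, none of which the protocol gives. Over the range shown, 3-month power runs from well below the cumulative test (30% against 69%) to well above it (about 95% against 45%). Late windows can hide a cumulative benefit or reverse it, slightly in the main example and only under early uptake and mostly short care. Moving the primary initiation time point to 12 months is therefore a trade-off, not a correction the documents compel. Because Secondary Outcomes and the Power Analysis point to a longer horizon and the Analytic Plan to 3 months, the choice should be made openly.

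**What to change.** 1. Add a prespecified between-arm analysis of first initiation since baseline: discrete-time time to first initiation over the four 3-month windows, with cumulative initiation by 3, 6, 9 and 12 months. Name it as the test of the 12-month hypothesis.
2. Label the 6-, 9- and 12-month results of the past-3-month item, and the categorical growth model, as current care use rather than initiation.
3. State whether the primary initiation time point is 3 or 12 months, with the reason.
4. Keep 3 months for the drinking and consequence outcomes.

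The four windows together cover the 12 months, so no new data are needed. The cost is one more analysis and a rule for missed visits. If 12 months is chosen, the primary initiation result also comes later.

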As concluded in a recent review of brief internet-based interventions for young adult alcohol misuse [50], from a public health perspective, being able to reach a large number of individuals and provide them with interventions that lead to even modest effects is beneficial at a societal level. Such modest effects from a single-session program may be important as an individual begins to evaluate one’s personal alcohol use and considers making a change, which may include seeking out formal assessment and more intensive treatment. The personalized normative feedback (PNF) approach offers a reference point for an individual’s personal drinking habits compared to peers, and similar to a checkup model [41,51], allows one to consider making a change to their drinking. Though PNF interventions are efficacious, these effects are often small and short-lived [52]. Thus, there is room for PNF interventions to expand beyond short-term effects on drinking and be used as a vehicle to connect those who have never received an intervention before with more intensive services. For veterans engaging in heavier problem drinking, sustained changes in drinking may be better obtained through in-person individual or group interventions, as opposed to a one-time brief intervention. For veterans who use alcohol to cope with or manage PTSD or depression symptoms, more intensive co-occurring disorder treatment may be indicated, whereby they can learn more adaptive techniques to cope with negative affect. In our pilot study, we found that almost twice as many PNF condition participants as control participants reported increases in motivation and likelihood to seek AUD treatment simply after viewing the PNF [53], alluding to the promise of the approach in targeting treatment initiation among the group of veterans who have not engaged in care or have had substantial barriers or challenges doing so. If the brief intervention prompted veterans to think more about making a change to their drinking, it may be a tool to reach those who may not have otherwise considered change and to connect them with services.

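### For the four drinking and consequence outcomes, 3 months is the primary time point, but the only stated arm test is on growth factors over 12 months, so no stated test targets the 3-month difference

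*Protocol article*

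**What the plan says.** All of this is in the Protocol article, Methods, Analytic Plan.

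- Primary time point (Overview): "The primary outcome time point for this trial will be the baseline to first follow-up (ie, 3 months post baseline". Later waves are of interest as well: "we are interested in the past 30-day changes from baseline to each of the 3 additional follow-up timepoints".
- Model for the primary and secondary outcomes: "a taxonomy of latent growth models will be estimated". Neither the growth shape nor the time coding is given.
- Arm test: "To assess between-group differences in the intercept and growth factors, we will regress each on a dummy variable".
- Treatment initiation has a categorical growth model, and the authors will "as well as estimate simple logistic regression at each time point".
- Cohen d is to be calculated "at all 4 follow-up time points for both between group and within group", as a measure of practical significance. No test is attached to it.
- Per-wave regressions of the primary outcomes appear once more, for moderators only: "To explore moderation, we will use simple linear regression models for primary outcomes at each time point".
- Power Analysis: 80% power, two-sided 0.05, for d=0.22 at 3 and 6 months and d=0.23 at 9 and 12 months.

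The Background section says of personalized normative feedback in general that "these effects are often small and short-lived".

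**The concern.** A primary time point matters only if a named test is tied to it. For the four drinking and consequence outcomes, the named test is on parameters that describe the whole trajectory. If time zero is baseline, the intercept is a pre-randomisation quantity. If the shape is linear, the slope summarises 12 months and is not the 3-month change.

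Three things are at stake. An early effect that fades could be tested by a parameter that barely responds to it. A late effect could make the trajectory test significant although little has happened at the declared primary time point. And because the shape comes from a family of models with no primary parameter named, the quantity that decides the trial could be settled after the data are seen.

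**Working it through.** **Step 1: which test does the stated power belong to?** For a two-group comparison at one wave with unit SD, n per arm = 2(1.960+0.842)²/d².

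- d=0.22: 2 × 2.8016² / 0.0484 = 324.3, so 325 per arm, which is 325/400 = 81% of those randomised.
- d=0.23: 2 × 2.8016² / 0.0529 = 296.7, so 297 per arm, which is 297/400 = 74%.
- With all 400 per arm, the detectable d would be 2.8016 × √(2/400) = 0.198.

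The stated figures therefore fit a separate group comparison at each wave after about 19% and 26% attrition. The article states no attrition, so the retention figures are an inference. The figures do not describe a growth-factor test.

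**Step 2: which stated tests reach the 3-month arm difference?**

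| Outcome | Stated arm tests | 3-month difference tested? |
|---|---|---|
| Drinking days, drinks per occasion, binge days, consequences | Growth factors on arm | Not by any stated test; Cohen d is descriptive |
| Treatment initiation | Growth factors on arm, and logistic regression at each wave | Yes |

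**Step 3: how much can it matter?** This is an expected-value generalised least squares calculation.

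- From the article: waves at 0, 3, 6, 9 and 12 months; 400 per arm; two-sided 0.05.
- Assumed: unit SD; exchangeable correlation ρ of 0.5 to 0.6; 19% of participants with baseline only, 7% followed through 6 months and 74% complete; no true baseline difference.

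For true arm differences δ, design matrix X and within-person covariance V, summed over dropout patterns p with n_p participants per arm:

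b = [Σ (n_p/2) X_p′V_p⁻¹X_p]⁻¹ Σ (n_p/2) X_p′V_p⁻¹δ_p, with the bracketed inverse as the covariance of b.

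Power = Φ(|b|/SE − 1.96) + Φ(−|b|/SE − 1.96).

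Standard errors for ρ=0.5 and 0.6 are 0.071 and 0.064 for the linear slope (per 12 months), and 0.077 and 0.069 for the 3-month change with time categorical.

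| True d at 3/6/9/12 months | Linear slope estimate | Slope power | Direct 3-month change power |
|---|---|---|---|
| 0.22/0.15/0.08/0 (fading) | −0.040, −0.042 | 9-10%, direction opposite to benefit | 82-89% |
| 0.22/0/0/0 (3 months only) | −0.079, −0.081 | 20-24%, direction opposite to benefit | 82-89% |
| 0.22 throughout (sustained) | 0.188, 0.186 | 75-83% | 82-89% |
| 0.055/0.11/0.165/0.22 (building) | 0.220, 0.220 | 87-93% | 11-13% |

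Further results from the same calculation:

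- **Fading effect, linear model.** With baseline as time zero, the expected intercept difference is about 0.10 although the true baseline difference is 0. The model-implied 3-month difference is 0.09 instead of 0.22.
- **Fading effect, quadratic model.** The joint test of the two growth factors has 77-86% power, but the implied 3-month change is 0.12.
- **3-month-only effect, quadratic model.** Joint power is 28-34%, and the implied change is 0.03.
- **Piecewise model with a knot at 3 months, first segment.** Power is 88-94% for the fading effect and 59-69% for the 3-month-only effect.
- **Categorical time with baseline arm means constrained equal.** The 3-month contrast has 90-94% power whenever the 3-month effect is 0.22.

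**The case against.** A reader might infer that the plan leaves its primary contrast untested altogether and will miss a short-lived effect. The article does not support that, for four reasons.

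- **Treatment initiation** is also a primary outcome and is tested at 3 months by logistic regression. For the other four outcomes, the 3-month Cohen d would at least display the effect.
- **The shape is not fixed as linear.** The 10% figure belongs to the least favourable of the shapes examined for a fading effect. Quadratic and piecewise models, which the wording equally allows, detect that effect well.
- **The time coding is not fixed either.** If time were centred at 3 months, the intercept would be a 3-month quantity. A latent-basis model with loadings 0 at baseline and 1 at 3 months has a growth factor that is the 3-month change, given a shape common to both arms. Leaving the arm-to-intercept path free costs precision but is not an error.
- **The article does not simply expect effects to fade.** The remark in Background concerns this class of intervention in general. This Study sets out to test 12-month outcomes, the hypotheses expect benefit at all four follow-ups, and Power Analysis cites small effects over 2 years in related studies.

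It can also be said that a condensed article may leave shape and coding to an analysis plan that is not shown. That is fair for those details. It does not remove the point, because the article itself states both a primary time point and an arm test, and for these four outcomes the two do not correspond. The 3-month contrast is left without a stated test; it is not ruled out.

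**Conclusion.** The point holds for drinking days, drinks per occasion, binge days and consequences. For these outcomes no stated test targets the declared 3-month difference, and the per-wave power statement belongs to a test that is not the one described. It does not hold for treatment initiation.

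The size depends on the growth shape eventually chosen and on the true time course. In the cases examined it runs from a small loss (sustained effect, linear slope 75-83% against 82-89%) to near-total loss of power (fading effect, about 10%). There is also the reverse risk of a significant slope with almost no effect at 3 months. These figures rest on the inferred retention, the assumed correlation, unit SD and a continuous-outcome approximation. The mismatch between time point and test rests on none of them.

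**What to change.** For each of the four outcomes, name the model-based arm difference at 3 months as the primary test. Preferably take it from one model of all five waves with time categorical and the baseline arm difference fixed at zero, using a count link where the outcome needs one. Take the 6-, 9- and 12-month contrasts from the same model, and make the growth factors a secondary description of the trajectory. State the power for that 3-month contrast, together with the retention it assumes.

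A piecewise growth model with a knot at 3 months, with the first segment regressed on arm, is an alternative closer to the present plan. It is weaker if the effect is present at 3 months only (59-69%).

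The cost is wording and model syntax; the data stay the same. The model carries a few more mean parameters than a straight line, and it has less power than a slope test if the effect builds up linearly. The change should be made before outcome data are analysed, so that the data do not choose the shape and the deciding parameter.
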